# Efficacy of compatible acupoints and single acupoint versus sham acupuncture for functional dyspepsia: study protocol for a randomized controlled trial

**DOI:** 10.1186/s13063-019-3875-5

**Published:** 2020-01-14

**Keywords:** Acupuncture, Compatible acupoints, Single acupoint, Functional dyspepsia, Randomized controlled trial

## Abstract

**Background:**

Acupoint selection is a key factor in the treatment of diseases and has not been well studied. The aim of this trial is to explore the differences in efficacy between compatible acupoints and a single acupoint for patients with functional dyspepsia (FD).

**Methods:**

This randomized controlled trial will be conducted in the First Affiliated Hospital of Changchun University of Chinese Medicine in China. Two hundred and sixteen FD patients will be randomly assigned to the compatible acupoints group, single acupoint group, or sham acupuncture group. This trial will include a 1-week baseline period, a 4-week treatment period, and a 4-week follow-up period. During the 4-week treatment period, patients will receive 20 sessions of acupuncture (weekly cycles of one session per day for 5 consecutive days followed by a 2-day break). The primary outcome will be a change in the Nepean Dyspepsia Life Quality Index from baseline to after the 4-week treatment period. Secondary outcome measures will include the dyspeptic symptom sum score, Overall Treatment Effect questionnaire, and 36-item Short Form survey. Adverse events also will be recorded. Ultraweak photon emission and metabolomics tests will be performed at baseline and at the end of treatment to explore the mechanisms of the differences between compatible acupoints and a single acupoint.

**Discussion:**

The results of this trial will allow us to compare the difference in efficacy between compatible acupoints and a single acupoint. The findings from this trial will be published in peer-reviewed journals.

**Trial registration:**

Acupuncture-Moxibustion Clinical Trial Registry, AMCTR-IPC-18000176, registered on 4 March 2019; Chinese Clinical Trial Registry, ChiCTR1900023983, registered on 23 June 2019.

## Background

Functional dyspepsia (FD) is a functional gastrointestinal disorder characterized by persistent upper dyspeptic symptoms without organic lesions [1]. According to the Rome IV Standard, FD is divided into two subgroups: epigastric pain syndrome (EPS) and postprandial distress syndrome (PDS) [1]. The prevalence of FD is between 8% and 12% according to a recent cross-sectional study [2]. FD has negative impacts on health and results in a high economic burden [3].

Currently, the treatment for FD mainly includes lifestyle adjustment [4], eradication of *Helicobacter pylori* [5], antacid drugs [6], and prokinetic drugs [7]. However, a standard management for FD has not yet been established, and satisfactory pharmacotherapy is also unavailable [8]. As a result, an increasing number of patients tend to seek complementary and alternative therapies, such as acupuncture [9].

In recent years meta-analyses have suggested that acupuncture could alleviate symptoms of dyspepsia, regulate related negative emotions, and improve the quality of life in patients with FD [10, 11]. However, the number of acupoints selected in these clinical studies has varied. Acupoint selection is a key factor influencing the effect of acupuncture therapy [12]. The aim of this trial was to explore the differences in efficacy between the use of compatible acupoints and a single acupoint for patients with FD.

## Method/design

### Study design

This is a parallel randomized controlled study conducted in the First Affiliated Hospital of Changchun University of Chinese Medicine in China. Two hundred and sixteen FD patients will be recruited and randomized into one of three groups in a 1:1:1 ratio of the compatible acupoints group, single acupoint group, and sham acupuncture group. The three phases include a 1-week baseline period, a 4-week treatment period, and a 4-week follow-up period. Figure 1 shows the flow diagram of the trial. The study will be conducted in accordance with the Declaration of Helsinki and has been approved by the Ethics Committee of the First Affiliated Hospital of Changchun University of Chinese Medicine (CCZYFYLL2018–011-1). We have registered in the Acupuncture-Moxibustion Clinical Trial Registry (AMCTR-IPC-18000176) and Chinese Clinical Trial Registry (ChiCTR1900023983). Written informed consent will be obtained from each participant before randomization. The Standard Protocol Items: Recommendations for Interventional Trials (SPIRIT) 2013 checklist [13] is provided in Additional file 1.

**Fig. 1 Fig1:**
[figure not shown]
Study flow chart

### Participants

#### Participation criteria

Participant inclusion criteria are as follows:
met the diagnostic criteria of Rome IV [1] for functional dyspepsiasigned the written informed consent formaged between 18 and 50 years old (either sex)had not taken a drug that may affect dyspepsia in the 15 days prior to the studynot participating in any other research

#### Exclusion criteria

Participant exclusion criteria are as follows:
dyspepsia symptoms caused by organic disease, metabolic disease, or drugsserious physical or mental diseases, such as cardiovascular diseases, lung diseases liver diseases, kidney diseases, and hematopoietic diseasesaggravated malignant tumors or other serious consumptive diseases, infectious diseases, or bleeding diseasesfear of acupuncture or infection related to the locations of ZuSanli (ST36) and ZhongWan (RN12)inability to cooperate with gastroscopy, severe anxiety, depression, or fear of dark spacespregnancy or lactation in women

### Recruitment, randomization, allocation concealment, and blinding

Notices will be published and distributed through advertisements, hospital websites, and notice boards. Research assistants will obtain signed written informed consent forms. Additional consent provisions for the collection and use of biological specimens will be provided to the participants. Participants will be randomly divided into the compatible acupoint group, the single acupoint group, or the sham acupuncture group in a 1:1:1 ratio. The randomization sequence will be generated with a random number table by an independent statistician. A sealed envelope will be used to hide the group assignments. Then, the envelopes will be numbered in sequential order from 1 to 216 and stored by a research assistant who does not take part in enrolling patients. When an eligible patient is enrolled into the study, an envelope will be opened by the research assistants who are responsible for enrolling the patients. The acupuncturists will not be masked due to the nature of acupuncture. However, participants, outcome assessors, and statisticians will be unaware of the group assignments. The participant’s allocated intervention will be not revealed until the statistical analysis is completed.

### Intervention

Participants will be randomly allocated into one of three groups: A, the compatible acupoints group; B, the single acupoint group; or C, the sham acupuncture group (control group). Two acupuncturists, who are from Chinese Medicine Practitioners in China and have at least three years of clinical experience in acupuncture practice, will perform all acupuncture sessions. Several training workshops will be provided prior to the commencement of the study to ensure that the skills of the acupuncturist are consistent. During the 4-week treatment period, patients will receive 20 sessions of acupuncture (4 weekly cycles of one treatment per day for 5 consecutive days, followed by a 2-day break). Sterile needles (0.25 mm × 40 mm/ 0.25 × 25 mm, Hwato, Suzhou, China) will be used in the trial. All acupuncture treatments and laboratory tests will be provided for free to improve adherence to the intervention protocol. Patient and acupuncturist signatures will be required after each acupuncture session to monitor adherence. Other treatments that may affect the dyspepsia symptoms will be prohibited, such as antacids, prokinetics, non-steroidal anti-inflammatory drugs, and antidepressant drugs.

#### Acupuncture groups A and B

Acupuncture will be applied at RN12 and bilateral ST36 in group A (compatible acupoints group) but will be applied only at RN12 in group B (single acupoint group). According to our previous reviews, ZuSanli (ST36) and ZhongWan (RN12) are the most frequently used compatible acupoints in gastrointestinal motility disorders [14, 15]. The acupoint locations are based on the “2006 People’s Republic of China National Standard” (GB/T1234–2006), and the acupuncture operation is based on the textbook of the 12th Five-Year Plan of the Ministry of Health. In particular, the skin will be cleaned with alcohol (75%), the sterile needles will be inserted perpendicularly 21–26 mm into the acupoints, and then they will be lifted and thrusted for de qi (a compositional sensation including soreness, numbness, distention, and heaviness). One auxiliary needle will be shallowly pricked in a position 2 mm away from the needle (proximal part). Each needle used for acupoints and their auxiliary needles will be connected to an electroacupuncture apparatus (Hwato SDZ-V Acupoint Nerve Stimulator, Suzhou Medical Co., Ltd.) for 30 min. The frequency will be 60/100 Hz, and the electric current will vary from 0.1 to 1.0 mA until the patients feel comfortable. The manipulation procedure is shown in Fig. 2

**Fig. 2 Fig2:**
[figure not shown]
Manipulation procedure.

#### Control group

The nonacupoint puncture to be used in group C is located in the medial arm on the anterior border of the insertion of the deltoid muscle at the junction of the deltoid and biceps muscles, and this is a location that has been used in several trials [16–18]. Then, the sterile needles will be perpendicularly inserted 21–26 mm into the acupoints but not for de qi. One auxiliary needle will be shallowly pricked in a position 2 mm away from the needle (proximal part). The electroacupuncture apparatus will be the same as the one used for the acupuncture groups.

### Outcomes

The following outcomes will be assessed by independent outcome assessors. These assessors will be trained before participating in this trial and will be blinded to the group assignments. The outcome assessors will contact the participants on the phone up to three times if the participants do not respond to the assessment. The outcome assessments will be performed at three time points: at baseline, at the end of the acupuncture treatments, and at the end of the follow-up period (Fig. 3). Patient privacy information will be separated from the trial data, and the analysis and publication of trial data results will not involve patient privacy information.

**Fig. 3 Fig3:**
[figure not shown]
Schedule of enrollment, intervention and assessments for this study protocol. NDLQI: Nepean Dyspepsia Life Quality Index; DSSS: dyspeptic symptom sum score; OTE: overall treatment effect; SF-36: 36-item short form survey; UPE: ultraweak photon emission

#### Primary outcome

The primary evaluation index in the trial will be the change in scores on the Nepean Dyspepsia Life Quality Index (NDLQI) from baseline through the 4-week follow-up period. The NDLQI [19] is a disease-specific scale of quality of life that includes four aspects: life interference (13 items), knowledge/control (seven items), drinking/eating (three items), and sleep/disturbance (two items). Each item contains five options, corresponding to 1 to 5 points. The sum score = 100-[(actual raw score − lowest possible raw score)/raw score range] × 100. Higher scores indicate a better quality of life.

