### Sample size

Based on our clinical experience, changes in the NDLQI scores in the compatible acupoint group, single acupoint group and sham acupuncture group at the 4th week are expected to be 12, 8, and 4, respectively. The standard deviations in the three groups are expected to be 10, 13, and 13, respectively. The two-sided significance level is 0.05.
$$ n=\frac{\psi^2\left(\sum {S}_i^2/k\right)}{\sum {\left({\overline{X}}_i-\overline{X}\right)}^2/\left(k-1\right)} $$

A sample size of 60 patients in each group is estimated to have 80% power to detect significant differences among the three groups. To compensate for a 20% loss to follow-up, the sample size was increased to 72 patients.

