### Statistical analysis

The intention-to-treat analysis will be used for all allocated participants in the baseline condition. Baseline characteristics will be summarized across the treatment groups. Missing values will be imputed by the last observation carried forward (LOCF) method. Depending on whether the data are normally distributed, the continuous variables will be described as the mean (standard deviation) or the median (interquartile range). One-way analysis of variance (ANOVA) will be used for comparisons among the three groups. Categorical variables will be described using frequency (percentage) and compared using Fisher’s exact test. The statistical analyses will be performed using SAS 9.1.3. *P* < 0.05 will be considered statistically significant.

All efficacy analyses, which will include all participants who are randomized, will be performed using the intent-to-treat analysis. Primary comparisons (change in the NDLQI scores at week 4 relative to the baseline scores among the three groups) will be made with ANOVA. Pairwise comparisons will use the Student-Newman-Keuls method.

For the secondary outcomes, continuous variables, including the DSSS and SF-36 scores, metabolomics, and UPE, will be compared among the three groups at all follow-up time points using ANOVA. The Student-Newman-Keuls method will be used for pairwise comparisons. The OTE and adverse events will be summarized for each group and compared using Fisher’s exact tests.

Analysis of covariance (ANCOVA) or logistic regression analysis will be used in the sensitivity analysis. The sensitivity analysis will also be performed using a per-protocol analysis, which includes only those who complete ≥16 sessions and have no major protocol violations (e.g., taking other drugs during the trial).

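### The primary endpoint is set at two different times: end of the 4-week treatment, and through the 4-week follow-up

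*Protocol article*

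**What the plan says.** Four places in the protocol article give a time for the primary endpoint.

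- **Outcomes, Primary outcome:** the change in NDLQI score "from baseline through the 4-week follow-up period".
- **Abstract, Methods:** "The primary outcome will be a change in the Nepean Dyspepsia Life Quality Index from baseline to after the 4-week treatment period".
- **Sample size:** the expected NDLQI changes in the compatible acupoints, single acupoint and sham groups "at the 4th week are expected to be 12, 8, and 4, respectively".
- **Statistical analysis:** "Primary comparisons (change in the NDLQI scores at week 4 relative to the baseline scores among the three groups) will be made with ANOVA".

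Study design sets out the phases: "The three phases include a 1-week baseline period, a 4-week treatment period, and a 4-week follow-up period". The opening paragraph of Outcomes schedules assessments at baseline, at the end of treatment and at the end of follow-up.

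**The concern.** The section that defines the primary outcome names a different period from the one used in the abstract, the sample size and the analysis. The two times are four weeks apart and measure different things. Week 4 gives the effect at the end of 20 sessions. The end of follow-up gives what remains four weeks after the last of them. Compatible and single acupoints could differ at one visit and not at the other.

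Three things are at stake:

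- **Choice of result.** Both values will be in the database. With two definitions in print, either could be presented as primary once the data are known, and each could be supported by citing the protocol.
- **Justification of size.** The expected changes of 12, 8 and 4 are stated for week 4. No mean or standard deviation is given for the end of follow-up. If the Primary outcome section governs, the primary endpoint has no sample-size basis.
- **Imputation.** Missing values are filled by last observation carried forward, with 20% loss to follow-up allowed for. For a patient lost between the two visits, the end-of-follow-up value would be the week-4 value repeated. The choice of visit therefore changes how much of the primary result is imputed.

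**Working it through.** **1. The four statements side by side**

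| Place | Time of the primary endpoint |
|---|---|
| Abstract, Methods | after the 4-week treatment (week 4) |
| Primary outcome | through the 4-week follow-up (4 + 4 = week 8 from the start of treatment) |
| Sample size | 4th week |
| Statistical analysis | week 4 |

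The follow-up period cannot be read as another name for the treatment period, because Study design lists the two as separate phases of four weeks each. The assessment schedule, which covers all the outcomes that follow it, has a visit at the end of each phase. Both candidate values will therefore be collected. The word *through* adds a further doubt: it could mean the value at the end of follow-up or the whole course up to then. Neither reading gives week 4 alone.

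**2. What the sample size supports**

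The protocol's formula is n = ψ² × (ΣSᵢ²/k) / [Σ(X̄ᵢ − X̄)²/(k − 1)].

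- ΣSᵢ²/k = (10² + 13² + 13²)/3 = 438/3 = 146
- Σ(X̄ᵢ − X̄)²/(k − 1) = [(12 − 8)² + (8 − 8)² + (4 − 8)²]/2 = 32/2 = 16
- ratio = 146/16 = 9.125

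With the large-sample ψ for two degrees of freedom, 80% power (ψ ≈ 2.195) gives 44 per group and 90% power (ψ ≈ 2.515) gives 58. The stated 60 per group is thus close to a 90% figure, not an 80% one. That is a separate matter and does not bear on this point. What matters here is that the means are stated only for the 4th week and nothing is given for any later time. No power can be computed for the end of follow-up.

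**3. Error rate if either visit may count as primary**

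Let Z₁ and Z₂ be the test statistics for one pairwise contrast at the two visits, each tested two-sided at 0.05, with correlation ρ between the change scores. Under no effect at either visit:

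P(at least one significant) = 1 − P(|Z₁| ≤ 1.96 and |Z₂| ≤ 1.96)

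The upper bound, under independence, is 1 − 0.95² = 0.0975. The protocol gives no value for ρ, so a range is assumed. The three-group test was simulated as a large-sample test with two degrees of freedom (4 million draws per value of ρ).

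| ρ (assumed) | One pairwise contrast | Three-group test |
|---|---|---|
| 0.5 | 9.1% | 9.1% |
| 0.6 | 8.8% | 8.9% |
| 0.7 | 8.3% | 8.4% |
| 0.8 | 7.8% | 7.9% |
| 0.9 | 7.0% | 7.1% |
| 0.95 | 6.5% | 6.5% |

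A smaller simulation of the actual ANOVA at 60 per group (20,000 runs) gave 9.2% at 0.5, 8.6% at 0.7 and 6.8% at 0.9, which agrees within simulation error.

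**The case against.** The best reply is that the operative analysis is already fixed. The Statistical analysis section names the primary test and ties it to week 4, and the sample size and abstract agree. No primary test is described at the end of follow-up. On this view the Primary outcome sentence is a drafting slip, and anyone who declared the later visit primary would contradict three other statements. The article is also loose with the term elsewhere: it promises comparisons of metabolomics and photon emission at all follow-up time points, although both are measured only at baseline and at the end of treatment.

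Much of this stands. Week 4 is very likely what was intended, and that makes the correction easy. It does not remove the contradiction, because the outlying sentence is in the section a reader consults for the definition of the endpoint, and no rule says which section prevails.

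The error rate is also fairly called conditional. It applies only if the visit is chosen after both results are known. Carrying week-4 values forward tends to raise the correlation, which moves the rate toward the lower rows of the table, but it stays above 5%.

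Blinding the statistician until the analysis is complete makes it harder to pick the visit that favours a particular arm. It does not prevent choosing between two masked p-values.

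The full protocol and the registry records may state a single time. They are not available here, and the published text contradicts itself whatever they say.

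**Conclusion.** The point holds and must be fixed. The document gives its primary endpoint two times and no reading reconciles them. This conclusion rests on the text alone.

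As to size, a primary result chosen from the two visits would carry a false-positive chance of about 8–9% in place of 5%, for correlations of 0.5 to 0.8, and about 6.5–7% for correlations of 0.9 to 0.95. These correlations are assumptions, and the figures describe what the wording leaves open, not any intention to select. Apart from the error rate, a primary endpoint at the end of follow-up would have no planning assumptions behind it.

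**What to change.** Amend the Primary outcome section so that the primary endpoint is the change in NDLQI score from baseline to the end of the 4-week treatment period (week 4). This matches the abstract, the sample size and the primary analysis. List the NDLQI change from baseline to the end of follow-up as a secondary outcome on durability. Date the amendment before unblinding and before any between-group comparison of NDLQI is seen; an amendment made later would not remove the doubt. Check both registry entries and align them if they differ.

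The cost is one sentence in an amendment and one added line among the secondary outcomes. It needs no new visit or data and leaves the planned sample size as it is. If the sponsor does intend the end of follow-up as primary, the abstract, the sample size and the primary analysis must all be rewritten, with expected means and standard deviations for that time.

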#### Secondary outcomes

##### Dyspeptic symptom sum score (DSSS)

The mean change of dyspeptic symptom sum score (DSSS) [20] from baseline is used to evaluate the severity level of four main symptoms: postprandial fullness, early satiety, epigastric pain, and epigastric burning sensation. Each symptom will be scored as follows: 0 (none), 2 (mild: spontaneous remission within 1 h after meal), 4 (moderate: ease within 1–3 h after meal), and 6 (severe: relief after > 3 h and/or treatment needed). All scores are added up to obtain a sum score between 0 and 24. Higher scores indicate more severe symptoms.

##### Overall treatment effect (OTE)

The mean change in the OTE [21] from the baseline will be evaluated, which is a questionnaire of 0–3 points as follows: 0 points for no relief or exacerbation, 1 point for mild relief, 2 points for obvious relief, and 3 points for complete relief.

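### The OTE outcome is defined as a change from baseline although the scale already rates relief, and it is then tested with Fisher's exact test, which fits neither that definition nor the ordered 0–3 categories

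*Protocol article*

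**What the plan says.** Protocol article, Secondary outcomes, Overall treatment effect (OTE): "The mean change in the OTE [21] from the baseline will be evaluated". The scale is printed as "0 points for no relief or exacerbation, 1 point for mild relief, 2 points for obvious relief, and 3 points for complete relief".

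Protocol article, Outcomes: "The outcome assessments will be performed at three time points: at baseline, at the end of the acupuncture treatments", with a third assessment at the end of follow-up. OTE is not exempted from the baseline assessment in the text. The schedule figure, which might show this, is not available here.

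Protocol article, Statistical analysis, on the remaining endpoints other than the primary: "continuous variables, including the DSSS and SF-36 scores, metabolomics, and UPE, will be compared among the three groups at all follow-up time points using ANOVA". OTE is not named in that list. Instead, "The OTE and adverse events will be summarized for each group and compared using Fisher’s exact tests". This follows the section's general rule: "Categorical variables will be described using frequency (percentage) and compared using Fisher’s exact test". The same section imputes missing values by LOCF and includes all randomized participants in the efficacy analyses. It names no ordinal method and no responder cut-off for OTE.

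**The concern.** Change from baseline suits the DSSS and the SF-36, which describe a patient's current state and can be measured before treatment. OTE is different. Each category states how much relief has occurred, so before the first session there is nothing to rate and nothing meaningful to subtract.

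The test then answers a different question from the one the definition poses. A mean change calls for a comparison of means. Fisher's exact test on three arms by four categories asks only whether the category proportions differ in any way, and it treats none, mild, obvious and complete as interchangeable labels.

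At stake is how the patient's global rating is reported and how well the trial can detect a difference on it. The lack of a real baseline value also matters for missing data, because LOCF needs an earlier value to carry.

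**Working it through.** **1. Definition against analysis.** The OTE section calls for a numerical score, a subtraction of baseline, and a mean. The Statistical analysis section calls for a count in each category and Fisher's exact test. The subtraction gives a defined result only if every patient is assigned 0 at baseline. The change then equals the post-treatment score, but the article does not state this convention, and Fisher's test still does not compare means.

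**2. Missing data.** A patient with an end-of-treatment rating who is lost later has a value to carry to the end of follow-up. A patient lost before the end-of-treatment rating has none. If a nominal baseline 0 were recorded, LOCF would enter that patient as having no relief or exacerbation. The sample size section allows for 72 − 60 = 12 losses per arm. It does not say when they occur, so within that allowance the number affected is anywhere from 0 to 12 per arm.

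**3. Fisher's test ignores order.** With fixed margins, the probability of a table is proportional to 1/∏ n_ij!, where n_ij is the count in arm i and category j. Rearranging the columns leaves this product, and so the p-value, unchanged. A hypothetical table with 60 per arm shows it (categories 0 to 3):

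- compatible acupoints: 12, 18, 22, 8
- single acupoint: 18, 20, 16, 6
- sham: 26, 20, 10, 4

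Fisher's test gives p of about 0.08 in the true order and with the categories scrambled (0.078 and 0.082; the gap is Monte Carlo noise). Kruskal-Wallis gives p = 0.005 in the true order and 0.51 when scrambled.

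**4. What this costs in power.** The protocol states no OTE distribution, effect or power, so there is no figure to reproduce and what follows is an illustration.

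- From the protocol: three arms, 72 randomized and 60 evaluable per arm (planned for the primary outcome, not for OTE), and "The two-sided significance level is 0.05".
- Assumed: three sham distributions over categories 0 to 3, namely 40/30/20/10%, 25/35/30/10% and 50/30/15/5%.
- Assumed effect: logit P(Y ≤ j | arm) = logit P(Y ≤ j | sham) − s·δ, with s = 0 for sham, 1 for single and 2 for compatible acupoints. δ = 0.35 or 0.50, so the odds ratio per step is exp(δ) = 1.42 or 1.65.
- Method: 600 simulated trials per setting, permutation Fisher test against Kruskal-Wallis.

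| Odds ratio per step | n per arm | Fisher | Kruskal-Wallis |
|---|---|---|---|
| 1.42 | 60 | 29–31% | 44–46% |
| 1.42 | 72 | 32–39% | 50–57% |
| 1.65 | 60 | 56–61% | 76–77% |
| 1.65 | 72 | 67–68% | 83–85% |

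Ranges are across the three sham distributions. Setting by setting, the smallest loss is 43.5 − 29.7 = 13.8 points and the largest is 76.3 − 55.8 = 20.5 points, or about 14 to 21. With no effect, both tests rejected in about 4–7% of trials, consistent with 5% given simulation error.

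Degrees of freedom explain the loss. The unordered test has (3 − 1)(4 − 1) = 6 and the rank test has 3 − 1 = 2. A noncentrality of 9.635 gives 80% power on 2 df and 62% on 6 df.

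**5. When the ranking reverses.** Take sham 40/30/20/10%, single 40/25/15/20% and compatible 40/20/10/30%. The ratios of compatible to sham are 1.0, 0.67, 0.5 and 3.0 across the categories, so the effect is not monotone across the scale: complete relief gains from mild and obvious relief, while the no-relief group is unchanged. At 72 per arm, an unordered test (chi-square in place of Fisher) has 69–70% power and Kruskal-Wallis 17%.

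**The case against.** The strongest reply is that the change-from-baseline phrase is stock wording shared with the DSSS and SF-36, and that the Statistical analysis section governs. That section keeps OTE out of the ANOVA list, treats it as categorical, and names a valid test. On this view only a wording repair is needed. Much of this stands, and it rules out several stronger readings.

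- A reader might infer that OTE cannot be analysed at all. The documents do not support that: the planned comparison of categories is computable, and a baseline of 0 for everyone would make the change equal to the rating.
- A reader might infer that the plan gives no direction or size of effect. It provides a summary per group, and frequencies with percentages show both. What it does not specify is a single effect estimate with an interval.
- A reader might infer that Fisher's test is invalid here. It is not, since its type I error is held.
- A reader might take the power loss as a property of this trial. It rests on assumed distributions and a proportional-odds shift, which favours a rank test, and step 5 shows the opposite is possible.
- A reader might infer that LOCF fails for OTE generally. It fails only for patients lost before the first post-treatment rating.

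The planned sensitivity analysis by ANCOVA or logistic regression does not settle the matter. It names neither OTE nor a cut-off, and does not say whether the logistic model is ordinal.

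What the reply does not remove is that the article states an endpoint and a test that do not match, and that the test discards the order built into the scale.

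**Conclusion.** The point holds as an inconsistent endpoint definition plus an avoidable loss of efficiency. The first part needs no assumption: it follows from the scale as printed and from the two sections read together. The size of the second, about 14 to 21 points of power at 60 to 72 per arm, depends on assumed sham distributions and an assumed monotone proportional-odds effect, and it can reverse otherwise. The LOCF gap is real but limited to early losses, whose number the protocol does not give. OTE is a secondary outcome for which the trial is not powered, so the primary NDLQI comparison is unaffected. The plan should be changed, but its main conclusion is not threatened.

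**What to change.** In the OTE section, define the outcome as the OTE rating at the end of treatment and at the end of follow-up, and drop the change from baseline. In the Statistical analysis section, compare OTE among groups with an ordinal method, choosing one of two before unblinding:

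- Kruskal-Wallis with pairwise Wilcoxon tests; or
- a proportional-odds model, if a common odds ratio with 95% CI for compatible versus single acupoint is to be reported. The rank tests do not give that odds ratio.

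State how patients with no post-treatment OTE rating are handled, since LOCF has nothing to carry for them. Keep the percentages per group, and keep Fisher's exact test for adverse events and other unordered categorical variables.

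The cost is a few sentences, with no new data and no change in sample size. The downside is lower sensitivity to non-monotone differences and, for the model, reliance on the proportional-odds assumption.
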